#### Feasibility

We believe recruiting 25 participants over the course of 2 years is feasible. Participants will be recruited through the Temerty Centre for Brain Intervention at CAMH, which treats approximately 150 to 200 patients with depression with electroconvulsive therapy per year. The principal investigator is a staff psychiatrist at the Mood and Anxiety Division, which provides outpatient services for a large population with mood disorders at local and provincial levels. In addition, this protocol has been piloted with 3 patients who were nonresponsive to electroconvulsive therapy, and the patients were able to comply with a protocol of 2 sessions per week for 8 treatment sessions given very close clinical supervision in a trial (unpublished data, [name]).

#### Consent to Participate

Informed consent will be obtained from each individual who agrees to participate in the trial prior to and throughout participation. Patients meeting criteria will be referred to the study coordinator to discuss the study purpose, procedures, potential risks, and rights as research participants. Consent forms describing the study intervention, study procedures, and risks will be given to each participant, and written documentation of informed consent will be required prior to completing the initial screening visit and starting the study intervention. Once consent is obtained, the research personnel will confirm that inclusion and exclusion criteria are met before proceeding with baseline testing. Patients will be informed that they can withdraw from the study at any point. A copy of the information and consent documents will be given to the participants for their records. The informed consent process will be documented, and the form signed before the participant undergoes any study-specific procedures. The rights and welfare of the participants will be protected by emphasizing to them that the quality of their medical care will not be adversely affected if they decline to participate in this study.

Data confidentiality and confidentiality of the identities of the individuals participating in this study will be strictly maintained. Data forms that include identifying information will be kept in locked cabinets. Only the unique ID number assigned by the research coordinator will be used to represent participants during data entry, data transfer, data analysis, or other file management procedures. All information linking their identity will be kept separate from the research records. All information entered into a computer will be stored in a password-protected encrypted file format on a secure server. If any participant withdraws from the study, any research information recorded for or resulting from participation prior to the date that the participant formally withdrew consent will continue to be stored and used (in the manner described above) for research purposes (and will be disclosed by the investigators); however, no new data will be collected. Withdrawing from the study will not have any consequences for the participant. Participants' identities will not be revealed in the publication or presentation of any results from this study.

### Intervention

#### Drug Characteristics, Distribution, and Storing

A sterile form of racemic ketamine hydrochloride will be dispensed through the CAMH pharmacy and will be administered intranasally using an atomizer provided by the pharmacy (MAD300, Teleflex). The CAMH research pharmacy will order the investigational product from the supplier (Sandoz Canada Inc) on behalf of the research team with the study investigator’s authorization and will be responsible for the receipt and responsible destruction of the investigational product. The investigational product will be stored between 15 ºC and 30 ºC, protected from light and heat and discarded within 28 days of initial use.

#### Drug Administration and Scheduling

Intranasal rketamine will be administered twice per week for 4 weeks (8 treatment sessions in total). The dosage schedule will be determined based on participants’ weight, clinical response, and tolerability (Multimedia Appendix 1). Given that the absolute bioavailability of intranasal ketamine is 45% to 50 % compared with that of intravenous administration [13,14], intranasal doses will range from 1 mg/kg to 1.6 mg/kg to represent usual intravenous doses of 0.5-0.8 mg/kg and to account for reduced bioavailability of the intranasal form. Participants will be started at the lowest dose during the first treatment session (average 50 mg of intranasal ketamine administered in 2 syringes with 25 mg per syringe).

#### Dose Adjustment

If the first session is tolerated well, and the patient has no side effects, the session 2 dose will be increased to 1 mg/kg (to represent an intravenous dose of 0.75 mg/kg adjusted to 50% bioavailability). If both sessions are tolerated well, session 3 will start on a full therapeutic dose (1.5-1.6 mg/kg to represent intravenous doses of 0.75-1 mg/kg). Participants will have a weekly visit with the study’s medical doctor, and doses will be monitored and adjusted based on tolerability and clinical response; however, they will not exceed 1.6 mg/kg.

#### Monitoring Schedule

All patients will stay on-site for the administration and 2-hour postintervention monitoring period, per consensus guidelines in ketamine administration [27]. Patients will be provided with a separate quiet space, noise-cancellation headphones, and an eye mask to minimize environmental disruptions. All patients will be observed 1:1 or 1:2 for the entire duration of the treatment session by trained personnel. The medical doctor is present on-site during the session to address any urgent requests and provide support to the team and patient. Vitals will be taken and recorded consistently during every 30 minutes during the 2-hour monitoring period after administration. A medical team will manage any emergencies that arise, and appropriate medications will be provided to manage treatment-related side effects and any adverse events, if needed (defined by clinical site policies and regulations). Clinical and neurophysiological assessments will be administered according to a schedule for study visits by trained research personnel (Multimedia Appendix 2).

#### Potential Risks and Mitigation Strategies

Given the potential risks described below, trained medical personnel will be present during the administration and for the entire duration of the 2-hour monitoring period.

Drug-related risks include (1) psychiatric symptoms such as fatigue, dizziness, anxiety, visual and auditory disturbances, panic attacks, increased irritability, or changes in mood and behavior; (2) medical symptoms such as transient increases in blood pressure and heart rate, an increase in need to urinate, headaches, vision changes, chest pain, shortness of breath, confusion, memory impairment, anaphylaxis; and (3) rare risk of dependency. Ketamine is classified as a schedule I controlled substance due to its potential for abuse and addiction and can be abused in a number of ways, including via injection, snorting, or orally [8]. Ketamine can produce vivid dreams and feel that the mind is separated from the body. Regular users of ketamine can become tolerant to the dissociative effects of the drug, meaning more and more is needed to achieve the same effect [8]. To address these risks, in this trial, ketamine will be dispensed by the research pharmacy and administered by a trained medical professional, and the patient will receive close supervision and monitoring. Doses are individually calculated, and treatment sessions are structured to prevent tolerance building. Patients will be strongly discouraged from using ketamine outside of the context of this trial and will be informed that if they have more questions, they can be discussed with their medical provider or study physician.

A potential risk in clinical assessments is that answering multiple questions can, at times, be distressing. These adverse reactions are primarily brief and transient and rarely have any long-term implications.

The ability of TMS to noninvasively stimulate brain areas presents a significant advance beyond techniques that require the invasive method of direct cortical or transcranial electrical stimulation. Magnetic fields pass through the scalp and skull without the impedance encountered by direct electrical stimulation, permitting enhanced control over the site and intensity of stimulation. In numerous studies [23,24], single-pulse TMS has been found to pose no significant health risk to properly screened healthy volunteers. Single-pulse TMS is now in routine clinical diagnostic use in hundreds of neurophysiological laboratories worldwide, and the induced electrical current is well below that which is expected to cause harm to nervous tissue; thus, stimulation at <1 Hz carries virtually no risk of seizure and is therefore classified as a nonsignificant risk device [23,24].

### Study Measurements

Given that this trial recruits participants who received at least one electroconvulsive therapy session, and therefore, underwent blood work, electrocardiography, and medical clearance by anesthesia services in accordance with standard clinical procedures, we will use these parameters for this trial. The results will be available for screening and review by the study’s medical doctor prior to the start of treatment. Tests completed within the 6 months prior to screening will be used unless new medical symptoms requiring further investigation emerge, in which case, the tests will be repeated. Blood tests will include complete blood count with differential tests (white blood cells, red blood cells, hemoglobin, hematocrit, mean corpuscular volume, mean corpuscular hemoglobin, mean corpuscular hemoglobin concentration, red cell distribution width, mean platelet volume, platelet, nucleated red blood cell count, neutrophil count, lymphocyte count, monocyte count, eosinophil count, basophil count) and blood chemistry tests for liver function (alanine aminotransferase, aspartate aminotransferase), kidney function (blood urea nitrogen, creatinine), electrolyte levels (sodium, potassium, chloride, phosphate), and thyroid function (thyroid-stimulating hormone). Electrocardiography results will be reviewed by the study’s medical doctor. Participant blood pressure will also be monitored before, during, and after treatment.

Clinical assessments will include (1) the Mini-International Neuropsychiatric Interview, to assess current and lifetime depression and other psychiatric disorders and to clarify psychiatric inclusion and exclusion criteria; (2) the 24-item Hamilton Rating Scale for Depression [28], as the primary outcome measure (and a score greater than or equal to 14 will be used to establish eligibility at study entry); (3) the Scale of Suicide Ideation [29], administered at baseline, weekly, at posttreatment, and at follow-up to monitor for any safety concerns and a secondary outcome measure to assess suicidality; and the(4) World Health Organization Disability Assessment Schedule 2.0 [30], used as a standard measure of disability promoted and administered at baseline and posttreatment to assess changes in individual level of functioning.

Demographic information, medical history, concomitant medications, and antidepressant treatment history form information will also be assessed.

Monitoring assessment during treatment sessions will include (1) vital signs collected every 30 minutes during a 2-hour monitoring session (blood pressure, heart rate, and oxygen levels) and (2) behavior changes assessed through observation.

Neurophysiological assessments will include (1) the Transcranial Magnetic Stimulation Adult Safety Screen to assess for potential TMS risk factors; and (2) TMS-EMG/EEG (Multimedia Appendix 2). Our neurophysiological measures have been established and have a high test–retest reliability (ie, intraclass correlation >0.9) [31,32]. Data analysis will be performed using semiautomated methods developed and validated by our group [31,32]. TMS pulses will be administered to the left dorsolateral prefrontal cortex, using a figure-of-eight coil (7 cm), and 2 Magstim 200 stimulators (Magstim Company Ltd) connected via a Bistim module, and motor evoked potential data will be collected using commercially available software (Signal, Cambridge Electronics). Each TMS session will include the establishment of the individual threshold for stimulation motor cortex, and dorsolateral prefrontal cortex localization will be performed according to previously published methods [31,32]. Resting motor threshold will be determined by applying single pulses of TMS to the motor cortex while the coil is placed at the optimal position to elicit motor evoked potentials from the right abductor pollicis brevis muscle. The resting motor threshold is defined as the minimum stimulus intensity that elicits a motor evoked potential of >50 μV in more than 5 of the 10 trials [33,34]. Electromyography will be recorded from the abductor pollicis brevis with Ag–AgCl electrodes placed over the belly of the muscle. The signal will be amplified (Intronix Technologies Corporation Model 2024F), filtered (bandpass 2 Hz-5 kHz), digitized at 5 kHz (Micro 1401, Cambridge Electronics Design), and stored in a laboratory computer for offline analysis. The participants will be instructed to relax throughout the study. Trials contaminated with voluntary muscle activity will be discarded.

EEG will be used to evaluate TMS-induced cortical evoked activity. EEG recordings will be acquired through a 64-channel EEG system [35]. A 64-channel EEG cap will be used to record the cortical signal, and 4 electrodes will be placed on the outer side of each eye and above and below the left eye for eye movement artifacts. All electrodes will be referenced to an electrode placed on the vertex positioned posterior to the Cz electrode. Direct current EEG signals will be recorded with a 20 kHz sampling rate and with a low-pass filter of 300 Hz, which, in pilot experiments [35], was shown to avoid saturation of amplifiers and minimize the TMS-related artifact. The EEG data will be downsampled to 1 kHz and segmented with respect to the TMS stimulus, such that each epoch includes 1000 ms of prestimulus baseline and 1000 ms of poststimulus activity. Epochs will be baseline corrected with respect to the TMS-free prestimulus interval (1000 ms to 110 ms prior to the TMS). The baseline-corrected poststimulus intervals (approximately 25 ms-1000 ms) that are not contaminated by TMS artifact will be extracted and digitally filtered using a zero-phase shift 1-100 Hz bandpass filter (48 dB per octave). Records will be manually reviewed at this stage, and trials contaminated with muscle activity, movement, and TMS artifacts will be excluded from further analysis. Finally, the average signals at each recording site will be computed from the movement-free epochs (approximately 80 trials per participant) and fed into an automated eye-blink correction algorithm [36]. The eye-blink corrected average EEG waveforms will be imported into MATLAB (The MathWorks Inc), and further analyses will be carried out utilizing the EEGLAB toolbox [37-39]. Further methods in this approach will be conducted according to previously published combined TMS/EEG studies [35].

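### Two stated signal settings need correcting: the EMG low-pass lies above half the sampling rate, and the EEG is cut to about 975 ms before a 1 Hz high-pass is applied

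*Protocol article*

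**What the plan says.** All the settings are in the protocol article, Methods, Study Measurements.

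- **EMG.** The signal is "filtered (bandpass 2 Hz-5 kHz), digitized at 5 kHz". One stated use is the resting motor threshold, defined by a "motor evoked potential of >50 μV in more than 5 of the 10 trials".
- **EEG acquisition.** "Direct current EEG signals will be recorded with a 20 kHz sampling rate and with a low-pass filter of 300 Hz". Then "The EEG data will be downsampled to 1 kHz and segmented with respect to the TMS stimulus". Every epoch runs from 1 s before the pulse to 1 s after it.
- **EEG processing order.** Epochs are baseline-corrected against a pre-stimulus window. After that, "The baseline-corrected poststimulus intervals (approximately 25 ms-1000 ms") judged free of pulse artifact are "extracted and digitally filtered using a zero-phase shift 1-100 Hz bandpass filter (48 dB per octave").

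Under Statistical and Analytical Plans, the neurophysiology analysis compares components of the TMS-evoked response at the left dorsolateral prefrontal cortex. No test of motor potentials is listed there. The Objective in the Abstract does name TMS electromyography along with EEG in the third outcome, and the Introduction plans short-interval cortical inhibition and intracortical facilitation with TMS-EMG and EEG.

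**The concern.** Both points are settings that the article states, not detail it leaves out.

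The EMG passband reaches twice the highest frequency that the sampling rate can represent. Whatever lies in the upper half of the band is folded down, and no later step can separate it from the signal. The EEG chain in the same section respects this limit: a 300 Hz low-pass against a 500 Hz limit at the 1 kHz working rate. The EMG figure is therefore either a misprint or an acquisition fault.

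In the EEG chain, a 2000 ms epoch is available, but only its post-pulse part is filtered. A steep filter with a 1 Hz lower edge responds over a long time. Near the cut it must use values that the segment does not contain, so the software's edge rule supplies them. The early components lie next to that cut, and evoked components are what the analysis section compares. The baseline subtraction comes before a filter that has zero gain at 0 Hz, so its effect may be lost.

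At stake are the noise in the motor potentials, and the accuracy and precision of an exploratory biomarker outcome.

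**Working it through.** The article gives no result of its own to reproduce here. The settings are from Study Measurements. The noise spectrum, filter family, padding and waveforms are assumptions.

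**EMG**

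1. Nyquist limit = 5 kHz / 2 = 2.5 kHz. The passband ends at 5 kHz, so 2.5 kHz of it (50%) lies above the limit.
2. With flat noise and an ideal filter, the SD ratio is √(5 / 2.5) = 1.41. With simulated white noise through Butterworth low-pass filters of order 2, 4 and 8, the aliased share of the sampled variance is 55%, 51% and 50%, and the SD ratio is 1.49, 1.43 and 1.42.
3. An assumed biphasic motor potential has practically no energy above 2.5 kHz, so its size and shape do not change.
4. Illustration: an assumed noise SD of 5 μV becomes 5 × 1.41 ≈ 7 μV. Over 20 ms there are 20 ms × 5 kHz = 100 samples. The expected range of 100 Gaussian samples is about 5 SD, so the peak-to-peak noise goes from about 25 to about 35 μV, still below 50 μV.
5. With the low-pass at 2 kHz, the aliased share falls to 13%, 2.6% or 0.2% (order 2, 4 or 8).

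**EEG: length and slope**

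1. Segment length = 1000 − 25 = 975 ms. One cycle at 1 Hz = 1000 ms.
2. A Butterworth filter falls by about 6 dB per octave per order. A slope of 48 dB per octave is therefore order 4 run forwards and backwards (4 × 6 × 2) or order 8 counted per pass (8 × 6). Both were tried.
3. For order 4 run both ways, 99% of the energy of the 1 Hz high-pass kernel spans about 1.46 s, longer than the segment.

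**EEG: effect on peaks.** The cut segment was filtered and compared with the same signal filtered in a long record.

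First assumed waveform, six peaks of about 2 to 8 μV between 30 and 280 ms, order 4:

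| Edge handling | 30 ms (3.54 on long record) | 60 ms (2.47) | 100 ms (−7.44) |
|---|---|---|---|
| Odd | 0.76 | 0.01 | −9.49 |
| Constant | 2.19 | 1.32 | −8.37 |
| None | 2.19 | 1.32 | −8.37 |
| Even | 3.62 | 2.63 | −7.26 |

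Across both orders the largest shifts are about 2.8 μV (odd), 1.4 μV (constant or none) and 0.7 μV (even). On the long record the peaks stay within about 0.1 μV of their true values.

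Second assumed waveform: a 60 ms peak of 3.64 μV on the long record reads 2.2 to 4.0 μV on the cut segment across orders and paddings. The low end is (3.64 − 2.2) / 3.64 ≈ 40%. Filtering the full 2 s epoch gives 3.5 to 3.8 μV, within about 4% of 3.64.

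The percentage depends on the waveform: the 60 ms peak almost vanishes in the first one under odd padding. The 40% is an illustration, not a bound.

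**EEG: baseline.** Baseline correction subtracts one constant per epoch and channel. Adding 10 μV to the segment before filtering changed the output by 0.0 μV with odd, even, constant and no padding. Under those rules the stated correction has no effect on the analysed waveform. The exception is software that extends the segment with zeros. There an offset becomes a step at the cut, and the correction does matter.

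**The case against.** **Edge handling is not stated.** An article may leave padding and filter implementation to the full protocol, and this one refers further methods to published TMS/EEG work. With even padding the shift is slight. A segment shorter than one cycle does not by itself make a filter fail. This stands: distortion is possible but not established. What the article does fix is the order of steps, and that order creates the dependence on padding.

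**The EMG effect is probably small.** It needs real noise between 2.5 and 5 kHz, the potential itself is unaffected, the threshold rule uses 10 trials, and no motor-potential test is listed. This stands as to size. The stated pair of figures is still wrong, and aliased data cannot be repaired.

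**The same linear pipeline applies at every visit.** A reader might infer that the cut produces a spurious change between baseline and follow-up. The documents do not support that. It would need edge values that differ systematically by visit, and nothing shows this. A reader might also suppose that slow residual pulse decay worsens the error. However, the article extracts only intervals free of artifact and excludes contaminated trials. Where decay remains, the full-epoch reading is not a true value either.

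**The measures are described as reliable** (intraclass correlation above 0.9) and the analysis methods as validated. Repeatability does not answer a question about amplitude, since a constant distortion is perfectly repeatable.

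**The remedy has edges too.** With order 8, the one-sided response to 99% of energy is 1148 ms. A 110 ms component has 1000 − 110 = 890 ms of epoch after it. This stands, and is why a longer record is preferable.

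**Conclusion.** The point holds in a limited form, as a minor correction. The EMG low-pass exceeds the 2.5 kHz limit. If the noise is flat, its SD is inflated about 1.4-fold, with probably little effect on the threshold. The EEG order of steps makes early amplitudes depend on an edge rule: the change is slight with even padding and roughly 40% of one assumed 60 ms peak with odd padding. It also makes the pre-stimulus baseline correction ineffective under edge rules that preserve a constant.

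It would go too far to say that the settings cannot work, or that the components are known to be distorted. The sizes rest on white noise, Butterworth filters and assumed waveforms. The accuracy and precision of an exploratory outcome in an open-label pilot are affected. No clinical, safety or feasibility conclusion is.

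**What to change.** **EMG.** Set the low-pass below 2.5 kHz, for example 2 kHz at 5 kHz sampling, with a steep enough slope. Alternatively keep 5 kHz and sample at more than 10 kHz. If the figure is a misprint, correct it. Check the actual setting before more data are collected, because aliased EMG cannot be recovered.

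**EEG.** Remove and interpolate the pulse-artifact window (to about 25 ms). Filter the full −1000 to +1000 ms epoch, or preferably a longer record, then baseline-correct and extract 25 to 1000 ms. State the edge handling, and use identical settings at every visit.

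**Cost.** One equipment setting, a reordered processing script with one added interpolation step, and possibly larger EMG files. EEG already recorded can be reprocessed if the raw data are stored.
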